### Recruitment {15}

Participant recruitment will be carried out by the referring entities in the catchment area of each participating hospital site. To achieve the target sample size, a sufficient number of referring entities must be involved. Therefore, the lead STATAMED physician at each intervention site is responsible for establishing a local network of referring entities to support recruitment. Lead STATAMED physicians will contact potential referring entities individually and inform them about the project. In addition, information events will be held, and public outreach (e.g. press releases, radio and TV interviews, and social media campaigns) will be used to raise general awareness of the project.

Referring entities must sign a contract to participate in STATAMED and obtain authorisation to refer patients. There is no minimum number of referring entities required per hospital as local conditions (e.g. population size and physician density) vary across sites. Each hospital is expected to recruit a sufficient number of referring entities to ensure that the required sample size is reached.

### Assignment of interventions: allocation

#### Sequence generation {16a}

The assignment of clusters to the time point when the transition phase starts will be randomised. However, an exception to randomisation is necessary at the beginning of the study. At the participating hospital sites, staff must be hired, and facilities need to be prepared before the intervention can begin. Thus, it must be ensured that at least one cluster at each participating hospital site is assigned to the intervention group at the beginning of the study. The selection of the first cluster at each site will be randomised.

The assignment of the remaining clusters in subsequent steps will follow a fully randomised approach, with the restriction that a maximum of one cluster per STATAMED ward will be assigned at each step. This restriction ensures that the number of participants per STATAMED ward develops evenly over the course of the trial.

These exceptions to randomisation are necessary to ensure the feasibility and acceptance of the research design at the STATAMED wards.

Randomisation will be based on computer-generated random numbers.

### Concealment mechanism {16b}

This is not applicable. Patients who meet the eligibility criteria and whose referring entity is located in a cluster assigned to the transition or intervention phase can participate in STATAMED. Before admission to a STATAMED ward, patients must provide informed consent to participate in the project.

The control groups will consist of patients who meet the eligibility criteria but receive treatment at a non-STATAMENT hospital. They will be identified retrospectively based on ICD-10 codes available in the claims data from the participating health insurers.

### Implementation {16c}

The allocation sequence will be generated through randomisation (see “Sequence generation {16a}”). The randomisation process will be conducted by the authors.

Participants will be enrolled at their respective STATAMED wards. Assignment to the intervention will depend on the cluster to which the referring entity is assigned. Patients who meet the eligibility criteria and whose referring entity is in a cluster currently in the intervention phase will be able to participate in STATAMED.

### Assignment of interventions: blinding

#### Who will be blinded? {17a}

This is not applicable. Blinding is neither possible nor required for the interventions evaluated in this trial.

### Procedure for unblinding if needed {17b}

This is not applicable. No procedure for unblinding is required, as neither participants nor STATAMED staff are blinded.

### Data collection and management

#### Plans for assessment and collection of outcome {18a}

Claims data from the statutory health insurers participating in the trial (AOK Rheinland-Hamburg and AOK Niedersachsen) will be used as the primary data source. Claims data are secondary data collected by health insurers for billing purposes and are considered reliable and valid. Because they reflect actual treatments provided by physicians and hospitals, they contribute to ensuring external validity. Matching methods will be applied in the analysis to improve comparability between the intervention and control groups, minimising selection bias [44].

To ensure data quality, data will be delivered at two time points by the participating health insurers. The final data delivery is expected at the end of the project period (approximately January 2027). Before this, a preliminary data delivery will take place (approximately June 2026) to check the completeness and plausibility of the data.

Although the outcomes will be measured using claims data, additional data will be collected to ensure the feasibility of the analysis. Table 1 provides an overview of the various data sources.

**Table 1 Tab1:** Data sources

Data set	Description	Utilisation
Claims data from participating statutory health insurers	Secondary data collected by statutory health insurers for billing purposes. The data set includes: patient master data (e.g., sex, year of birth, postal code), outpatient data (e.g., pseudonymised physician number, diagnoses[ICD codes], procedures, billed services), medicines (e.g., ATC code, issuance date, price/amount of reimbursement), inpatient data(e.g., hospital number, diagnoses [ICD-code], procedures, date of inpatient admission and duration of hospital stay, billed case rates)	Measuring primary andsecondary outcomes
Task documentation data	STATAMED-specific tasks performed by the lead STATAMED physician, mobile nurse, and case manager must be documented (e.g., mobile nurses document tasks performed during follow-up care, such as measuring vitalsigns or taking blood samples)	Allows assessment and comparison of implementationacross different STATAMED wards
Information on referring entity	Identification numbers and postal codes of referring entities	Allows assignment of patientlevel claims data to the correct cluster
Data according to §21 KHEntgG	Data provided by hospitals with STATAMED wards, including structural data (e.g., type of hospital, number of beds, number of nursing staff, number of physicians) and performance data (e.g., patient information [age, gender,residence], admission date, discharge date, diagnoses [ICD codes], procedures, billed services)	Measuring length of hospital stay for participants not enrolled with aparticipating health insurer

### Plans to promote participant retention and complete follow-up {18b}

Analyses will be based on claims data that are automatically collected when patients use medical services that are covered by the participating statutory health insurers. For this reason, no measures to ensure follow-up are required.

Patients are free at any time to withdraw their consent to participate in the study. In such cases, their data will be excluded from analysis.

STATAMED wards are equipped and staffed to treat patients who meet the eligibility criteria with appropriate, high-quality care. However, if a patient’s medical condition worsens or additional diagnostics are required during treatment, he or she will be transferred to another hospital that can provide the appropriate care. In such cases, data can still be used for analysis unless participants explicitly withdraw their consent.

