### Who will take informed consent? {26a}

Informed consent from trial participants in the intervention group will be obtained during the admission process at the STATAMED wards.

The three control groups consist of patients who meet the eligibility criteria but receive treatment at non-STATAMED hospitals. The control groups will be identified using claims data from the participating statutory health insurers. The evaluation of outcomes in the control groups will be based on routinely collected claims data, which the participating statutory health insurers provide independently of the study. The claims data will be anonymised, and no informed consent is required for these groups.

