### Sample size {14}

The required sample size was estimated prior to project implementation using Bonferroni correction to account for multiple comparisons because the trial includes two co-primary outcomes without a hierarchical structure: (1) length of hospital stay and (2) 30-day hospital readmission. Applying a type 1 error rate of *α* = 5%, the Bonferroni correction results in a per-outcome significance level of α/2 = 2.5% for confirmatory testing.

Sample size calculations were performed according to Woertman et al. [38]. Based on existing literature [39] and a pre-analysis of claims data, a minimum relevant difference of 15% was specified for both co-primary outcomes. An intra-class correlation coefficient (ICC) of *ρ* = 0.05 was assumed to account for within-cluster correlation [40, 41], resulting in a design effect estimate of 0.61.

For co-primary outcome (1), the required sample size was estimated at 2331 participants; this increases to 2681 participants after adjusting for a 20% drop-out rate. For co-primary outcome (2), the required sample size was estimated at 3724 participants, rising to 4481 after applying the same drop-out assumption. Given that both outcomes are co-primary, the larger of the two estimates (i.e. 4481 participants) was initially adopted as the required sample size for the intervention group across all clusters over the full duration of the study.

These initial calculations relied on conservative assumptions, including a high estimated drop-out rate and the use of the Bonferroni correction for multiple comparisons. However, evidence from the literature and ongoing implementation experience allow for the following refinement of these assumptions.

Based on recent experience with implementation logistics and recruitment patterns, a more realistic drop-out rate of 15% is now assumed. In addition, Leppin et al. [42] conducted a meta-analysis that found an 18% reduction in the risk of readmission. Complex interventions and interventions ensuring structured follow-up care are found to be particularly effective in reducing readmission. Because both elements are core features of STATAMED, an effect size of 20% is considered plausible.

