### Statistical methods

#### Statistical methods for primary and secondary outcomes {20a}

The two co-primary outcomes (length of hospital stay, 30-day hospital readmission rate) are treated as continuous variables. The secondary outcomes (utilisation of hospital emergency departments, emergency outpatient care, and nonemergency outpatient care, as well as place of discharge) are also continuous except for the place of discharge (home, care facility, other), which is categorial.

Because there are two co-primary outcomes without hierarchical ordering, a correction for multiple testing is required. A Bonferroni correction will be applied, resulting in a one-sided significance level of α/2 = 2.5% for each primary outcome given a global type I error rate of *α* = 5%. However, the Bonferroni method is known to be conservative. As an alternative, the Romano-Wolf procedure [43] may be used, as it more efficiently controls the family-wise error rate by accounting for the dependence structure among outcomes through resampling (see “Sample size {14}”).

When analysing stepped-wedge designs, it is important to account for temporal effects given that each cluster transitions to the intervention in a stepwise fashion. In this study, this is particularly important because the STATAMED wards will gain experience with implementing the intervention over time. Additionally, the longitudinal design of the study necessitates the consideration of calendar time because patient case mix may vary by season (e.g. winter versus summer) due to the focus of the study on general medical conditions. To account for these temporal effects, generalised linear mixed models (GLMMs) and generalised estimating equations (GEEs) will be applied [45–47]. Propensity score matching, considering age, gender, and morbidity, will be used to ensure comparability between the control and intervention groups.

To avoid bias from patients who are transferred to other hospitals during STATAMED treatment or those who meet eligibility criteria but prefer to be treated at a non-STATAMED hospital, the analysis will be conducted according to the intention-to-treat and per-protocol principles [48].

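### Withdrawing consent removes a patient's whole record from the analysis, and this can happen only in the STATAMED group

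*Protocol article*

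**What the plan says.** All references are to the protocol article.

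- **Withdrawal rule, section {18b}.** "Patients are free at any time to withdraw their consent to participate in the study". The next sentence gives the consequence: "In such cases, their data will be excluded from analysis". The trigger is consent to participate. Nothing separates this from permission to use claims data, and nothing limits the exclusion to data after the withdrawal date.
- **Who consents, section {26a}.** "Informed consent from trial participants in the intervention group will be obtained during the admission process at the STATAMED wards". The three control groups are identified from insurer claims: "The claims data will be anonymised, and no informed consent is required for these groups".
- **Analysis principle, section {20a}.** Partly because of transfers out of STATAMED, "the analysis will be conducted according to the intention-to-treat and per-protocol principles".
- **Transferred or deteriorating patients, section {18b}.** "In such cases, data can still be used for analysis unless participants explicitly withdraw their consent".
- **Patients who decline services, section {11a}.** Some patients may turn down case-manager or mobile-nurse services. The section makes no distinction within the intervention group on that ground.
- **Data capture, sections {18b} and {20c}.** Claims accrue automatically and independently of the study, so the article sees no need for retention measures.
- **Drop-out, section {14}.** The initial allowance was 20% ("this increases to 2681 participants after adjusting for a 20% drop-out rate"). In the update, "a more realistic drop-out rate of 15% is now assumed". No cause is given that ties either figure to withdrawal of consent.

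**The concern.** Intention-to-treat keeps a patient in the group entered, whatever happens afterwards. Here a patient can leave the analysed set after entry, and only from one side of the comparison: a control patient gives no consent and so has none to withdraw.

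Timing adds to this. Consent is taken at admission, the post-hospital phase runs up to 28 days after discharge (section {13}), and withdrawal is possible at any time. A patient may therefore withdraw after a long stay or a readmission has already occurred, so the exclusion can follow the outcome.

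The lost information is also avoidable in part. The insurer holds the claims whether or not the patient stays in the project. A patient who wants to end participation, but does not object to use of the claims, has complete outcome data that the present wording discards. Matching on age, gender and morbidity (section {20a}) cannot bring an excluded patient back.

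At stake is a bias of unknown sign and size in both co-primary outcomes. Without a record of withdrawals, its possible extent could not be shown afterwards.

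**Working it through.** The plan gives no figure for withdrawal or its effect, so there is none to reproduce. The check has two parts.

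**1. The passages side by side**

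| Event | Where | Stays in the analysis? |
|---|---|---|
| STATAMED patient declines a service | {11a} | Yes, no distinction is made |
| STATAMED patient worsens and is transferred | {18b} | Yes, unless consent is explicitly withdrawn |
| STATAMED patient withdraws consent to participate | {18b} | No, without limit of time or scope |
| Control patient | {26a} | Yes, there is no consent to withdraw |

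Only the third row departs from intention-to-treat, and it has no counterpart among controls.

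**2. How large the bias could be**

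Assumed inputs, since the document gives neither:
- *w*, the share of STATAMED patients who withdraw consent: 1%, 2% and 5%.
- *k*, the mean outcome of withdrawers relative to the mean of all STATAMED patients: 1.5 and 2, with 1 and 0.5 as contrasts.

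Input from section {14}: a planned relative effect of 15%, updated to 20%.

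Let the mean over all STATAMED patients be *m*, and let there be no true effect. The mean of those retained is (*m* − *wkm*)/(1 − *w*). The apparent relative change is therefore

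(1 − *wk*)/(1 − *w*) − 1 = −*w*(*k* − 1)/(1 − *w*).

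The baseline cancels, so the formula serves either co-primary outcome.

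| *w* | *k* = 1.5 | *k* = 2 |
|---|---|---|
| 1% | −0.005/0.99 = −0.5% | −0.01/0.99 = −1.0% |
| 2% | −0.01/0.98 = −1.0% | −0.02/0.98 = −2.0% |
| 5% | −0.025/0.95 = −2.6% | −0.05/0.95 = −5.3% |

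At *k* = 1 the change is zero for every *w*. At *k* = 0.5 and *w* = 5% it is +2.6%, against STATAMED.

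Relative to the initial 15% difference, the largest value in the table is 5.3/15, about a third. At 2% withdrawal it is at most 2.0/15, about an eighth.

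**Dilution.** If the intention-to-treat set is defined by cluster phase, it also contains patients treated elsewhere (control group 2), who cannot withdraw. If, as an assumption, half the set is treated in STATAMED, the withdrawn share halves. For *w* = 5% and *k* = 2 the change is then −0.025/0.975 = −2.6%.

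**The case against.** The strongest reply is that the article already protects the patients one would worry about. Those who decline services stay in the group, and those who deteriorate and are transferred stay in by default. Pressure to withdraw also looks low, since outcome measurement asks nothing of patients. All of this stands, and it confines the point to explicit withdrawals.

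Second, stopping use of data after consent is revoked may be a legal duty. That stands too. It does not justify excluding someone who ends participation without revoking data use, which the present wording also covers.

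Third, withdrawal forms, counts and sensitivity analyses often sit in a fuller protocol or analysis plan that is not shown. This is fair for the counts and the sensitivity analysis. The exclusion rule itself, however, is stated in the article, and without qualification.

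Some stronger inferences are tempting, and the document does not support them:
- *The intention-to-treat analysis is broken.* At 1–2% withdrawal the illustrated bias is about 2% or less, against a planned 15–20%.
- *The data are deleted.* The text speaks only of exclusion from analysis.
- *The 15% drop-out measures withdrawal.* At *w* = 15% the formula gives −0.075/0.85 = −8.8% and −0.15/0.85 = −17.6%, which would rival the planned effect. But section {14} attributes the 15% to implementation logistics and recruitment patterns. Other sections describe other routes of loss: missing or inconsistent billing data and transfer of wrongly admitted patients ({20c}), and withdrawal of hospitals or referring entities ({10}).
- *Withdrawers do worse.* This is plausible for some, but nothing in the document shows it.

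**Conclusion.** The point holds in a limited form. Section {18b} fixes an exclusion after enrolment that can act in the STATAMED group only, can follow the outcome, and is wider than revocation of data permission requires. This departs from the intention-to-treat principle in section {20a}.

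The size cannot be derived from the document. Under the assumed *k* of 1.5 to 2, the apparent reduction with no true effect is about 0.5% to 2% at 1–2% withdrawal and 2.6% to 5.3% at 5%. It is smaller if the analysis set is defined by cluster phase, nil if withdrawers are average, and reversed if they do better. This is a worthwhile and cheap improvement to a stated rule. It is not evidence that the result will be materially biased.

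**What to change.** In section {18b}, replace the single exclusion sentence with two cases:

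1. A patient who ends participation without revoking permission to use data stays in the STATAMED group, and claims through day 30 after discharge are analysed.
2. Data are excluded only on explicit withdrawal of data permission, to the extent that the consent and data protection law require. State whether data from before the withdrawal may be kept.

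Record which case applies at the time of withdrawal. The evaluators receive anonymised data, so the ward or insurer should hold this record. Report the number excluded by site and period.

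Add a bounding sensitivity analysis for both co-primary outcomes as the article defines them: length of stay, and the continuous readmission measure that combines number and length of stays. Assign excluded patients unfavourable values in one run and favourable values in another. Counting them simply as readmitted would fit neither outcome.

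The cost is wording in the protocol and on the withdrawal form, a record of each withdrawal, and a small extra analysis. Patients who have already withdrawn under the current wording may have to stay excluded. They can still be counted and covered by the bounds.

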### Data management {19}

Data will be transferred in encrypted form from the health insurers to the evaluators. Only authorised project members will have access to the data. Data will be stored on a secure research server, with backups made on a regular basis. All steps in data preparation and analysis will be fully documented. Raw data will be stored separately from the processed study data to ensure the replicability and integrity of the results. Data will be archived for 10 years after the study has ended.

### Confidentiality {27}

Data will be provided in anonymised form, and it will not be possible for the researchers to identify individual patients. As a result, no patient-identifying information will be reported in any publications.

### Plans for collection, laboratory evaluation, and storage of biological specimens for genetic or molecular analysis in this trial/future use {33}

This is not applicable. No biological specimens will be collected in this trial.

### Statistical methods

#### Statistical methods for primary and secondary outcomes {20a}

The two co-primary outcomes (length of hospital stay, 30-day hospital readmission rate) are treated as continuous variables. The secondary outcomes (utilisation of hospital emergency departments, emergency outpatient care, and nonemergency outpatient care, as well as place of discharge) are also continuous except for the place of discharge (home, care facility, other), which is categorial.

Because there are two co-primary outcomes without hierarchical ordering, a correction for multiple testing is required. A Bonferroni correction will be applied, resulting in a one-sided significance level of α/2 = 2.5% for each primary outcome given a global type I error rate of *α* = 5%. However, the Bonferroni method is known to be conservative. As an alternative, the Romano-Wolf procedure [43] may be used, as it more efficiently controls the family-wise error rate by accounting for the dependence structure among outcomes through resampling (see “Sample size {14}”).

When analysing stepped-wedge designs, it is important to account for temporal effects given that each cluster transitions to the intervention in a stepwise fashion. In this study, this is particularly important because the STATAMED wards will gain experience with implementing the intervention over time. Additionally, the longitudinal design of the study necessitates the consideration of calendar time because patient case mix may vary by season (e.g. winter versus summer) due to the focus of the study on general medical conditions. To account for these temporal effects, generalised linear mixed models (GLMMs) and generalised estimating equations (GEEs) will be applied [45–47]. Propensity score matching, considering age, gender, and morbidity, will be used to ensure comparability between the control and intervention groups.

To avoid bias from patients who are transferred to other hospitals during STATAMED treatment or those who meet eligibility criteria but prefer to be treated at a non-STATAMED hospital, the analysis will be conducted according to the intention-to-treat and per-protocol principles [48].

